### **11.2.6 Recording and reporting of device deficiencies**

All device deficiencies will be documented throughout the study. The investigator at each site will be responsible for managing all device deficiencies and determine and document in writing whether they could have led to a serious adverse device effect.

All device deficiencies that might have led to a serious adverse device effect(s) if: suitable action had not been taken; intervention had not been made, or if circumstances had been less fortunate, must be reported to the Sponsor as for SAEs/SADEs.

### 11.2.7 Reporting of Pregnancy

Study participants will not routinely be tested for pregnancy as part of the trial follow up process. Any pregnancy which does occur during the course of the study should be reported to the Sponsor as indicated in section 11.2.5 immediately. It is at the investigator's discretion to decide whether the individual should be instructed to stop study treatment. All pregnancies that occur during trial treatment, or within seven days of finishing treatment, need to be followed up until completion and reported separately.

### 11.2.8 Healthcare arrangements and compensation for adverse events

Healthcare arrangements for subjects who suffer an adverse event as a result of participating in the study may include advice from clinical members of the study team or the patient's treating diabetes team, or use of emergency health services.

If an adverse event occurs, there are no special compensation arrangements unless this was due to the negligence of one of the clinical investigators or due to harm resulting from study protocol design. In this case subjects may have grounds for legal action for compensation. The normal national complaints mechanism will be available. In addition, any harm arising due to study design (both negligent and non-negligent) will be covered under Sponsor's insurance policy as applicable.

## 11.3 Anticipated adverse events, risks and benefits

### 11.3.1 Risks and anticipated adverse events

Known risks represent hazardous situations which may result in anticipated adverse events. In the following text, where appropriate, the term "risk" and "anticipated adverse events" are used interchangeably without affecting meaning.

### 11.3.2 Hypoglycaemia and hyperglycaemia

Subjects with type 1 diabetes have a pre-existing risk for hypoglycaemia and hyperglycaemia. Potential risks are:

- Risk of mild to moderate hypoglycaemia and associated symptoms such as sweating, trembling, difficulty thinking and dizziness. There is also a rare risk of severe hypoglycaemia when conscious level is altered, needing help from a third party to correct the hypoglycaemia. These risks are pre-existent in any patient with type 1 diabetes and the study objective is to develop systems to minimise these risks

- Risk of possible mild to moderate hyperglycaemia similar to the risk that a subject with type 1 diabetes experiences on a daily basis
- Risk of hyperglycaemia leading to diabetic ketoacidosis (DKA). This risk is pre-existent in any patient with type 1 diabetes.

### 11.3.3 Blood sampling

Subjects will be required to have nine blood tests (venepuncture) during the whole study. Those participating in the extension phase will have an additional two fasting blood tests. Venepuncture is required annually as part of the annual review for people with diabetes, and in some places venepuncture is required every 3 to 12 months for assessment of HbA1c. Potential risks include:

- Slight discomfort or bruising at the site (common)
- Excess bleeding at the site (unlikely)
- Infection at the site (rare)

Local anaesthetic cream or spray may be used to minimise the discomfort.

### 11.3.4 Finger-prick blood glucose measurements

Finger-prick tests may produce pain and/or bruising at the site.

### 11.3.5 Insulin injection therapy

Potential risks associated with multiple daily injection therapy include:

- Slight discomfort at the time of insulin injection (common)
- Slight bruising at the site of injection (common)
- Bleeding at injection site (rare)
- Infection at the site of injection (rare)
- Insulin pen malfunction and mechanical problems (rare)
- Allergy to insulin (very rare)
- Lipodystrophy / lipoatrophy (very rare)

### 11.3.6 Insulin pump therapy

Potential risks associated with insulin pump therapy include:

- Slight discomfort at the time of insertion of the insulin delivery cannula (common)
- Slight bruising at the site of insertion (common)

- Bleeding at insertion site (rare)
- Infection at the site of insertion (rare)
- Allergy to the insulin delivery cannula or adhesive (rare)
- Infusion set and cannula occlusions (rare)
- Insulin pump malfunction and mechanical problems (rare)
- Allergy to insulin (very rare)
- Lipodystrophy / lipoatrophy (very rare)

### 11.3.7 Continuous glucose monitoring

Potential risks associated with CGM:

- Slight discomfort at the time of insertion of CGM (common)
- Slight bruising at the site of insertion (unlikely)
- Bleeding at insertion site (rare)
- Infection at the site of insertion (rare)
- Allergic reaction to the CGM sensor material (rare)

If a skin reaction is classified as severe (the observation is noticeable and bothersome to subject and may indicate infection or risk of infection or potentially life-threatening allergic reaction), an adverse event form will be completed.

### 11.3.8 Questionnaires, interviews and focus groups

As part of the study, Participants will complete semi-structured interviews, focus groups and questionnaires which include questions about their private attitudes, feelings and behaviour related to diabetes. It is possible that some people may find these questionnaires to be mildly upsetting. Similar questionnaires have been used in previous research and these reactions are uncommon. If questionnaire or conversational responses indicate serious psychological distress as judged by the investigators, appropriate clinical services will be arranged. Any treatment will be documented in the case-report form.

The study team takes the safeguarding of children very seriously and should any concerns be raised during the course of the study, including during the interview and focus group sessions, these concerns will be dealt with in accordance with local policy. Participants and caregivers will be made aware of this.

### **11.3.9 Risk Analysis and residual risk associated with the investigational device**

A detailed risk analysis for the closed loop system was conducted, according to Cambridge University Hospitals NHS Foundation Trust's standard Risk Assessment Tool. The risk analysis is presented in a separate risk analysis report

The hazard analysis has identified two hazardous situations in which the residual risk assessed exceeds a predefined score after all practicable control measures have been applied. Risk/benefit analyses concerning these hazardous situations have been conducted by experienced and knowledgeable multidisciplinary members of the research team.

The risks/benefit analysis concluded that day and night closed loop is expected to reduce substantially but not to eliminate the risk of plasma glucose levels below 2.0 mmol/l. This is supported by clinical data recorded over more than 100 nights at the clinical research facility, by more than 9 years of total use of closed loop in home settings, by simulations, and is further enhanced by the requirement for a calibration check to be performed every day before breakfast and before evening meal.

## **11.4 Benefits**

It is expected that day and night closed loop system may have an important role in the management of diabetes. Therefore, the results of this study are likely to be beneficial for subjects with diabetes.

It is possible that subjects will not directly benefit from being a part of this study. However, it is also possible that the blood sugar information from the CGM devices along with the information about insulin dosing during day and night closed loop will be useful for subjects' diabetes self-management.

## **11.5 Data Monitoring and Ethics Committee (DMEC)**

An independent Data Monitoring and Ethics Committee (DMEC) will be informed of all serious adverse events and any unanticipated adverse device effects that occur during the study and will review compiled adverse event data at periodic intervals.

## 12 Methods and assessments

### 12.1 Procedures

#### 12.1.1 Height, weight and blood pressure

These will be recorded during the recruitment visit, at the 12 month and 24 month visits. Weight will be also measured at Visit 2 (Baseline Visit) and Visit 7 (6 months) before conducting the MMTT. Height will be measured in centimetres using a calibrated stadiometer. Weight will be measured in kilograms using a calibrated electronic scale. Blood pressure readings will be obtained using automated calibrated BP monitors with the patient seated comfortably for 5 minutes prior to the measurements.

Those participating in the extension phase will have height and weight measured at 36 and 48 months.

#### 12.1.2 Mixed Meal Tolerance Test (MMTT)

MMTT will commence following an overnight fast (from midnight; water permitted). Long-acting insulin or basal rates (for closed loop participants) will continue as normal. Rapid-acting insulin or bolus can be given up to 2 hours before the MMTT to correct for hyperglycaemia (subjects will use their own correction factors). The MMTT will only be performed if participant's blood glucose level is between 4 and 11.1 mmol/l or otherwise will be rescheduled.

Participants will be given a liquid meal according to bodyweight - Sustacal/Boost (Nestle, Switzerland, 17g carbohydrates, 4 g proteins, 3g fat per 100ml) or similar. Venous blood samples for the measurement of C-peptide and plasma glucose will be collected 10 minutes prior to the meal (-10 min), at the time of ingestion (0 minutes), and at 15, 30, 60, 90 and 120 minutes.

If the glucose level at t=120 minutes is >8 mmol/l, a subcutaneous insulin correction dose may be given, either via injection or pump, according to the subject's own insulin sensitivity factor. If the glucose level at t=120 is >14 mmol/l, ketones will be tested by finger prick. If ketones are >0.6 mmol/l, glucose and ketones will be repeated until ketones have decreased <0.6 mmol/l. Following the MMTT the participant will be offered a meal, before leaving the study facility.

#### 12.1.3 Continuous subcutaneous glucose monitoring

Two different continuous glucose monitoring systems (CGM) will be used throughout this trial: a blinded CGM with retrospective sensor glucose data read out, and a real-time system providing a contemporaneous display of sensor readings.

205761\_Protocol\_V8.0\_10 September 2019

### **12.1.3.1 Blinded Continuous Subcutaneous Glucose Monitoring**

Blinded CGM will be intermittently applied at various periods throughout the trial. During run-in, blinded CGM will serve to gain knowledge of the specific subject's glucose control characteristics before the beginning of any intervention arm. Post-randomisation, blinded CGM will be periodically used following 3-monthly study visits. Participants of both intervention arms will be fitted with a blinded sensor during the study visits (or 2 weeks prior to the study visit) and will wear the sensors until expiry or detachment. Sensors will be returned to the research team thereafter. Secondary glucose endpoints as outlined in 10.2 will be based on glucose data derived from data captured during these up to 14 day periods. Moreover, this data could be used to facilitate insulin dose optimisation during control intervention.

Subjects in the control intervention arm already using a FreeStyle Libre continuous glucose monitoring system will be able to use their own sensor, rather than the study blinded sensor.

Subjects participating in the extension phase will wear a blinded CGM following 12-monthly study visits.

### **12.1.3.2 Real-time Continuous Subcutaneous Glucose Monitoring**

Real-time CGM will be applied during closed loop intervention only. The control algorithm will use the real-time CGM's continuous stream of glucose data to control insulin titration. Data from the real-time CGM system will be downloaded periodically by the participant and during study visits.

### **12.1.4 Insulin pump data**

Data from the study insulin pump will be downloaded periodically by the participant and during study visits.

## **12.2 Human factors assessment**

We are broadly referring to human factors as the cognitive, emotional, and behavioural characteristics of the participants in the study. The human factors assessment battery is grounded in two principles: 1) it is critical to use evidence-based methods that are reliable, valid, and have parallel forms for youth and their caregivers, and 2) both quantitative (i.e., surveys) and qualitative (i.e., interviews, focus groups) data need to be gathered to provide the richest, most comprehensive characterization of the sample and their response to the closed loop system and clinical trial.

### **12.2.1 Questionnaires**

Surveys and tests used in this trial are listed in Table 3. The Measure column lists the construct of interest in bold. Participants/guardians will complete the questionnaires at time-points as indicated in the table. Additionally, feedback questionnaires on closed loop specific experience will be distributed to participants/guardians who have been randomised to the closed loop intervention arm. All results will be evaluated at the end of the study.

**Table 3.** Human Factors Assessment.

| Measure                                                     | Respondent         | Construct Measured / Relevant Points                                                                                                                                                                                                                                                                                                         | Duration | Time-point                                                               |
|--------------------------------------------------------------------|---------------------------|-----------------------------------------------------------------------------------------------------------------------------------------------------------------------------------------------------------------------------------------------------------------------------------------------------------------------------------------------------|-----------------|---------------------------------------------------------------------------------|
| Paediatric Quality of Life Inventory (PedsQL) Diabetes (38) | All youth and all parents | All youth ages 10-18 will complete age-appropriate PedsQL Diabetes module. There are 28 items total and can take up to 5 minutes to complete. Parents will also complete a proxy version.                                                                                                                                                           | 5-10 min        | Baseline,
12 months,
24 months

(Extension phase: 36 and 48 months) |
| Strengths and Difficulties Questionnaire (SDQ) (39)         | All youth and all parents | This is a widely used 25 item self-report inventory behavioural screening questionnaire for children and adolescents. The same 25 items are included in questionnaires for completion by the parents.                                                                                                                                               | 5-10 min        | Baseline,
12 months,
24 months

(Extension phase: 36 and 48 months) |
| Hypoglycaemia Fear Survey (HFS) (40-42)                     | All youth and all parents | Validated questionnaires (HFS child version, HFS parent version) to measure several dimensions of fear of hypoglycaemia. They consist of a 10-item “Behaviour subscale” that measures behaviours involved in avoidance and over-treatment of hypoglycaemia and a 13-item “Worry subscale” that measures anxiety and fear surrounding hypoglycaemia. | 5- 10 min       | 12 months,
24 months

(Extension phase: 36 and 48 months)              |

|                                                      |                                               |                                                                                                                                                         |            |                                                                                      |
|------------------------------------------------------|-----------------------------------------------|---------------------------------------------------------------------------------------------------------------------------------------------------------|------------|--------------------------------------------------------------------------------------|
| Cognitive testing
(CogState) (43)          | All youth                                     | Selected subtests from this computerised-cognitive testing battery will be completed electronically. See 12.2.2                                         | 15-20 min  | Baseline,
12 months,
24 months                                                 |
| Pittsburgh Sleep Quality
Index (PSQI) (44) | All youth and
all parents                  | The PSQI is a validated 19 item questionnaire that holistically assesses sleep quality and sleep duration.                                              | 5-10 min   | 6 months,
12 months,
24 months
(Extension
phase: 36
and 48
months) |
| INSPIRE                                       | Youth and
parents in
closed loop
arm | Measures the psychological side of automated insulin delivery. Child (6-12) and Adolescent versions (13-18) have 18 items; Parent version has 21 items. | 5 – 10 min | 12 months,
24 months
(Extension
phase: 36
and 48
months)              |
| PAID-Teen                                     | All youth                                     | Measures 26 items related to the daily hassles of managing type 1 diabetes, and the degree of diabetes distress that arises from diabetes management.   | 5 – 10 min | 12 months
24 months
(Extension
phase: 36
and 48
months)               |

### 12.2.2 Computerized cognitive testing

Participants will complete selected subtests from a computerized test battery, Cogstate (43), at baseline, 12 and 24 months. Cogstate has demonstrated sensitivity to subtle changes in cognition and is designed to accommodate repeated assessment of a single individual. The subtests selected, Identification Task, Two Back Task, Set-Shifting Task and the Continuous Paired Associate Learning Task measure choice reaction time, working memory, mental flexibility and fluid reasoning, and spatial new learning respectively. These skills are known to be sensitive to dysglycaemia (2; 4). Each task takes between 2 and 5 minutes to complete (total testing time 15-20 minutes). Raw data will be transferred electronically in an anonymised format (i.e using a numerical study identifier) to Cogstate for scoring and collation prior to electronic transfer back to the study investigators for statistical analyses.

### 12.2.3 Measures of sleep quality

Quality, duration and fragmentation of sleep will be assessed subjectively (using the Pittsburgh Sleep Quality Index (PSQI) or similar validated questionnaire, and a daily sleep diary) and objectively (by actigraphy) in participants, as well as subjectively in parents/carers (using the Pittsburgh Sleep Quality Index (PSQI)). These measures will be conducted over 7 days at 6, 12 and 24 months post diagnosis during both intervention arms.

The PSQI is a validated 19 item questionnaire that holistically assesses sleep quality and sleep duration. The sleep diary will record time of going to bed and waking, plus time of, and reason for (e.g. urination or infant feeding) any nocturnal awakenings.

An Actiwatch (Philips Respironics, Bend, Oregon, USA) worn on the non-dominant wrist will provide objective measures of sleep and wakefulness based on motor activity - a low cost, non-invasive and objective method for evaluating sleep in free-living participants. Actiwatchs will record time in bed and actual sleep time, as well as changes in sleep quality from measures of sleep maintenance, sleep efficiency, sleep latency, fragmentation index, total nocturnal activity, and percentage moving time. Light exposure will be measured by the Actiwatch's photovoltaic sensor.

### 12.2.4 Qualitative assessment

#### 12.2.4.1 Interviews

An integrated qualitative sub-study aims to explore parents' and youth's views about using closed loop systems; understand the impact of using closed loop systems on diabetes management practices and everyday family life; identify parents' and youth's information and support needs when using closed loop systems.

In-depth interviews will be undertaken at or after 12 months with a subset of at least 15 – 20 youth and at least 15 – 20 parents in the closed loop arm. Purposive sampling will be used to ensure diversity in terms of (a) youth's age and gender (b) parents' occupation/education and (c) family forms. Where possible, parents and youth from the same family will be interviewed. Participants will be interviewed separately unless a joint interview is requested.

#### **12.2.4.2 Focus groups**

Focus groups will be conducted at the end of the study (24 months). We will conduct focus groups at each of the study sites. Recruitment will proceed on a heterogeneous composition basis in terms of both randomisation and adult/children participants, in order to maximise the possibility of exploring relevant topics from different perspectives. Four families will be recruited for each focus group, with each participating family consisting of a child and either one or two parents, thus giving a total of between 8 and 12 participants per focus group. Two families in each group will include children randomised to pen MDI, with the remaining two families including children randomised to the closed loop system. Eligible families will be approached for focus group recruitment as soon as the participating child has participated in the study for 12 months; the focus groups will then take place in each study centre as soon as four families have agreed to participate. Minimal demographic details (gender and age) will be collected from participating individuals. We will work from a script of open-ended questions used to gather feedback and reactions to study recruitment and randomisation, study support systems, and the closed loop system. There will also be time for discussion of content raised by participants. Use of a moderator with advanced training will ensure consistency across groups. The moderator will keep time and manage group logistics. Sessions will be digitally audio-taped and transcribed by a trusted professional transcription service.

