##### 7.6.4 Focus Groups

Focus groups will take place at 24 months with participants and their parents (8-12 participants per group, from both study arms) at each of the study sites. A script of open ended questions will be used to gather feedback and reactions to study recruitment and randomization, study support systems, and the closed loop system. There will also be time for discussion of content raised by participants. The analysis will be conducted by [name].

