| 2. Multiple daily injections (control arm)                   | 
Participants in the control group will receive additional training sessions following randomisation including a refresher on carbohydrate counting skills, and insulin dose adjustments.
 
Standard therapy (i.e. MDI) will be applied for 24 months. Participants will be allowed to switch to insulin pump therapy if clinically indicated.
                                                                                                                                                                                                                                                                                                                                                                                                                                    |
| Follow up assessments (3-, 6-, 9-, 12-, 15-, 18-, 21-months) | 
Both arms. Follow up study visits will be conducted 3 monthly including data downloads/recording of insulin requirements, adverse event recording, and blood sampling (HbA1c).
 
Participants will be fitted with blinded CGM systems at the end of each follow up visit. The sensors will be worn at home for up to 14 days and will be sent back to the research team.
 
MMTTs will be performed at 6 month and 12 month follow up visits.
 
Sleep will be assessed using a wristwatch device for 7 days following study visits at 6 and 12 months post diagnosis. Concomitantly, a sleep diary and sleep quality questionnaire will be distributed.
 
Validated questionnaires evaluating the impact of the technology on quality of life, life change,
 |

|                                             |                                                                                                                                                                                                                                                                                                                                                                                                                                                                                                                                                                                                                                                                                           |

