## 9.12 End of study visit (Visit 14)

The subject will be invited to attend the research centre approximately 3 months after visit 12. This would be the end of 24 month study period. The subject will have a MMTT and a blood sample for HbA1c, immunological analyses and lipid profile will be taken. Body weight, height and blood pressure measurements will be made. Subject will be asked to complete questionnaires as outlined in section 12.2.1. Cognitive function will be assessed using validated computerized cognitive tests (see section 12.2.2). Additionally, subjects/family members will be invited to attend focus group discussions at their clinical site (see section 12.2.4.2) following the End of study visit. For participants of the closed loop intervention, who are not continuing with the extension phase, study device data will be downloaded and subjects will start transition to usual care.

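### Protocol 12.2.4.2 gives focus groups two incompatible timings; its scheduling sentence lets mixed-arm groups meet before the 24-month assessments

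*Combined protocol and SAP*

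**What the plan says.** Protocol 12.2.4.2 first fixes the timing: "Focus groups will be conducted at the end of the study (24 months"). Later in the same paragraph it sets out how groups are formed: "Eligible families will be approached for focus group recruitment as soon as the participating child has participated in the study for 12 months", after which "the focus groups will then take place in each study centre as soon as four families have agreed to participate".

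Each group has four families. On composition the section says "Two families in each group will include children randomised to pen MDI", and the other two families come from the closed-loop arm. The script is meant to "gather feedback and reactions to study recruitment and randomisation, study support systems, and the closed loop system".

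Every other place that mentions the groups puts them at the end of the 24-month period:

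- Protocol 9.12: "subjects/family members will be invited to attend focus group discussions at their clinical site (see section 12.2.4.2) following the End of study visit".
- SAP 7.6.4: "Focus groups will take place at 24 months with participants and their parents (8-12 participants per group, from both study arms").
- The end-of-study row of the synopsis, and the Visit 14 rows of Tables 1 and 2. Neither table lists a focus group at an earlier visit.

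On control-arm treatment, the synopsis says "Participants will be allowed to switch to insulin pump therapy if clinically indicated". Section 9.7.2 adds that NICE criteria apply.

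**The concern.** A site that wants to know when to hold its group is sent by section 9.12 to 12.2.4.2. There it finds one sentence naming month 24 and a more detailed procedure that triggers the meeting on the fourth family's agreement. Both cannot be followed.

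The choice matters because the groups mix the arms by design and discuss the closed-loop system. If a group meets before Visit 14, control families hear closed-loop users' accounts while open-label treatment and the 24-month assessments are still ahead. Three things could be touched:

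- **Questionnaires at 24 months.** SAP section 15.1 compares PedsQL, SDQ, HFS, PAID-Teen and PSQI between arms. Self-reports in an open-label trial are the outcomes most easily moved by such a conversation.
- **Pump uptake in the control arm.** SAP 5.2 removes controls who start a pump from the 24-month per-protocol set, so any influence on uptake also changes who is analysed.
- **The extension decision**, which is taken at 24 months and determines who contributes to the 36- and 48-month comparisons.

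The 24-month C-peptide, HbA1c and CGM results could follow through behaviour or treatment changes. Any such influence would come from the trial's own procedure, so it can be avoided.

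**Working it through.** No figure in the plan is disputed. The only number attached to the groups reproduces: 4 families × (1 child + 1 parent) = 8, and 4 × (1 child + 2 parents) = 12, which matches the stated 8 to 12 people. The sample size is a calculation for the 12-month endpoint and does not enter here.

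**Step 1. The timings side by side.**

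| Place | When the group meets |
|---|---|
| Protocol 12.2.4.2, opening | End of study, 24 months |
| Protocol 12.2.4.2, scheduling sentence | When four families agree, approached from 12 months in the study |
| Protocol synopsis, end-of-study row | 24 months |
| Protocol Tables 1 and 2 | Visit 14 |
| Protocol 9.12 | After the end-of-study visit |
| SAP 7.6.4 | 24 months |

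One entry out of six disagrees, and it is the only one that tells a site what triggers the meeting.

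**Step 2. Could the rule still give month 24 in practice?** For all four children to have reached 24 months, the last-enrolled of the four must have done so. That family can be approached at 12 months, so the fourth agreement would have to come 24 − 12 = 12 months after it could first be asked. Nothing in the section implies such a delay.

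**Step 3. Illustration of the likely timing.** Assumptions: even accrual over the full 2.5 years (30 months) of enrolment in protocol section 22, consecutive enrollees at a site, and prompt agreement.

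- 96/7 = 13.7 per site: 30/13.7 = 2.2 months apart, so four enrollees span 3 × 2.19 = 6.6 months.
- 15 per site: 30/15 = 2.0, span 6.0 months.
- 20 per site: 30/20 = 1.5, span 4.5 months.

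The group would then meet with its last family at month 12 and its first at about month 16.5 to 18.6. Refusals, or waiting for two families per arm, would push this later. These figures show only that a meeting before Visit 14 is a realistic result of the rule.

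**Step 4. What lies before the exposure.** The primary endpoint and the three key secondary endpoints are at 12 months. A visit on schedule falls by about day 365 + 14 = 379 after diagnosis. If time in the study runs from consent, taken up to 21 days after diagnosis, the earliest approach is between about day 365 and day 365 + 21 = 386. SAP 6.1 accepts a meal test up to day 420, so the possible overlap is between 420 − 386 = 34 and 420 − 365 = 55 days. It concerns only late tests in children whose group has already met.

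**Step 5. What lies after it.** The 24-month outcomes, the 24-month per-protocol set, and the extension decision.

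**The case against.** The strongest reply is that the intended design is clear. Five of six statements say 24 months, and the 12-month sentence can be read as recruitment logistics under the section's opening line. That is probably what the authors meant. It does not resolve the text, because the sentence does not stop at recruitment: it also says when the group takes place.

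Second, the routes to harm are limited. A pump switch needs clinical indication under NICE criteria, so a family's wish is not enough. The closed-loop system is supplied by the study to the intervention arm, so a control who switches gets a pump and not the intervention. Switchers stay in intention-to-treat follow-up, and follow-up generally continues after treatment withdrawal. All of this stands and narrows the concern. It does little for self-reported outcomes.

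Third, the focus group is not the only contact. The trial is open-label, and the peer-support scheme in section 9.20 is not restricted by arm. This also stands, with the difference that peer support is freely chosen by the family, whereas here the protocol itself convenes a mixed group.

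A reader might infer something stronger: that the comparator is contaminated, with 7 sites × 2 control families = 14 of 48 controls (29%) exposed. The documents do not support this. They give no number of groups per site, no sign that every group would meet early, and nothing to show that attendance changes treatment or outcomes. No 24-month power is stated against which a dilution could be judged.

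**Conclusion.** Wrong as written: the timing rule contradicts itself within protocol 12.2.4.2 and contradicts the synopsis, Tables 1 and 2, section 9.12 and SAP 7.6.4. This rests on the text alone and needs no assumption.

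The consequence is a possible bias, not a demonstrated one. It is confined to 24-month secondary outcomes, chiefly the questionnaires, control-arm pump uptake and the per-protocol set, and to the extension decision. The 12-month primary and key secondary endpoints are essentially outside it, apart from the possible overlap with a late meal test. The size of any effect cannot be derived from the documents. The point still merits a change, because the risk comes from the trial's own procedure and is cheap to remove.

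**What to change.** Replace the scheduling sentence in protocol 12.2.4.2. State that families may be approached from 12 months in the study, but that each group is held only after all four participating children have completed Visit 14 and their 24-month meal test, CGM and questionnaire data have been collected. The data condition is needed as well as the visit: section 9.11 allows Visit 13 to be combined with Visit 14 for families who continue, so the 24-month sensor wear and sleep questionnaire can fall after Visit 14.

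Keep the mixed-arm composition. The section gives a reason for it, namely hearing different perspectives, and correcting the timing does not require changing it.

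If any group has already met earlier, record its date and who attended, and examine the 24-month results by attendance. This would be descriptive, since attendance is not randomised.

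The cost is one sentence in the protocol, and some groups meet later because they wait for the last of the four children. SAP 7.6.4 needs no change of timing and no sample size is affected. One limit remains: for families in the extension, a group held after Visit 14 still precedes the 36- and 48-month assessments.
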